#### Estimation of impact of PAL alone and PAL + IHP interventions versus control

The calculations presented below use an alpha level of 2.5 % rather than the conventional 5 % to allow for 2 primary comparisons (PAL + IHP versus control and PAL alone versus control).

Exactly the same 3-stage sampling procedure will used as for the baseline survey, except that now 14 households will be selected from each village (total 11,340 households: 3,780 per study arm). As before, all eligible participants in each selected household will be interviewed, giving a total sample of 11,340 × 2.4 = 27,216 individuals (9,072 per study arm); 10 % of these individuals (2,721 in total: 907 per study arm) will be expected to show evidence of chronic cough-/wheeze.

The available evidence indicates that approximately 5 % of symptomatic individuals in the control group post-intervention will have a diagnosis in their health passport. The PAL + IHP intervention will be considered clinically important if it increases the proportion of symptomatic individuals with a registered diagnosis from 5 to 20 %.

With 9 clusters per group and 907 symptomatic individuals per study arm (100 per cluster), this study will have 80 % power to detect a clinically important difference between the PAL + IHP and control groups provided the BCV (between-clusters CV (coefficient of variation)) does not exceed 62.9 %, and will have 90 % power if the BCV does not exceed 54 %.

BCV measures the extent to which the proportion of symptomatic individuals with a registered diagnosis varies between the clusters, and expresses this as a percentage of the average proportion of symptomatic individuals with a registered diagnosis across all clusters combined. In most community interventions, BCV is usually less than or equal 25 % [27] so, even at worst, this element of the study will have over 90 % power.

The PAL alone intervention will be considered clinically important if it increases the proportion of symptomatic individuals with a registered diagnosis from 5 to 10 %. With 9 clusters per study arm and 100 symptomatic individuals per cluster, the study will have 80 % power to detect a clinically important difference between the PAL alone and control groups provided the BCV does not exceed 24.1 %, and 90 % power if the BCV does not exceed 13.7 % (so the actual power of this element of the study is expected to be at, or close to, 80 %). A summary of sampling steps and estimated numbers for the post-intervention survey is shown in Additional file 2: [name] Additional file 2.pdf,233 K.

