Assuming that 5 % of individuals who demonstrate symptoms of chronic cough-/-wheeze will have a diagnosis of CAD or TB in their health passport, a sample of 453 individuals will provide an estimate of the true health burden prevalence in each individual study arm with a precision of ±2.00. Ignoring clustering effects, the 1360 individuals in all 3 study arms combined will provide a precision of ±1.17 %; adding a design effect size adjustment of 2 to allow for clustering effects, the combined sample will have a precision of ±1.64 %.

(N.B. The effects of clustering within households, within villages and within health centre catchment areas will all be fully adjusted for in the statistical analysis using multi-level modelling methods). A summary of sampling steps and estimated numbers for the baseline survey is shown in Additional file 1: [name] Additional file 1.pdf, 235 K.

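### The between-cluster variation of at most about 25 % behind the power statements does not fit the design effect of 2 used for the same outcome at baseline, and the PAL-alone power of about 80 % depends on it

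*Protocol article*

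**What the plan says.** The protocol article makes two separate allowances for clustering of one outcome, the proportion of symptomatic people with a diagnosis of CAD or TB in their health passport.

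- **Baseline survey.** With 1,360 symptomatic people in 27 clusters and an assumed proportion of 5 %, it widens the confidence interval: "adding a design effect size adjustment of 2 to allow for clustering effects, the combined sample will have a precision" of ±1.64 %.
- **Estimation of impact (follow-up survey).** Here clustering enters through the BCV. PAL + IHP versus control has 80 % power up to a BCV of 62.9 % and 90 % up to 54 %. PAL alone has 80 % up to 24.1 % and 90 % up to 13.7 %. The section then cites a usual BCV of 25 % or less in community interventions. From this it concludes for PAL + IHP "so, even at worst, this element of the study will have over" 90 % power, and for PAL alone "so the actual power of this element of the study is expected to be at, or close to" 80 %.

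The two allowances are never linked. The opening of the sample size section calls the assumptions preliminary and based on expert opinion, and says they will be revisited once baseline data are in.

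**The concern.** A design effect and a BCV describe the same thing, variation between clusters, on different scales. Once the proportion and the cluster size are given, one follows from the other. Outcome, clusters and assumed proportion are the same in both sections, so the two allowances should agree.

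PAL alone versus control is one of two primary comparisons and has no margin: its power is already 79 % at a BCV of 25 %. If clustering is stronger than that, the chance of missing a real rise from 5 to 10 % is well above the roughly 20 % that the protocol implies. A null result could then be taken as evidence that PAL does not work.

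**Working it through.** **Inputs.**
- Significance level 0.025 per comparison: "The calculations presented below use an alpha level of 2.5 % rather than the conventional 5" %. Sidedness is not stated; two-sided (z = 2.2414) reproduces the protocol's figures.
- c = 9 clusters per arm, m = 100: "With 9 clusters per study arm and 100 symptomatic individuals per cluster".
- p0 = 0.05: "approximately 5 % of symptomatic individuals in the control group post-intervention will have a diagnosis in their health passport".
- p1 = 0.10 for PAL alone: "increases the proportion of symptomatic individuals with a registered diagnosis from 5 to 10" %.
- p1 = 0.20 for PAL + IHP: "increases the proportion of symptomatic individuals with a registered diagnosis from 5 to 20" %.
- Baseline cluster size 1,360/27 = 50.4; design effect 2.

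**Step 1: reproduce the stated limits.** Hayes-Bennett formula for unmatched clusters, with the same BCV k in both arms:

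(c − 1)(p1 − p0)² = (2.2414 + z_power)² × V, where V = [p0(1 − p0) + p1(1 − p1)]/m + k²(p0² + p1²).

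- PAL alone, 80 %: V = 8 × 0.0025/(2.2414 + 0.8416)² = 0.002104; k² = (0.002104 − 0.001375)/0.0125; k = 24.2 % (stated 24.1).
- PAL alone, 90 %: k = 13.8 % (stated 13.7).
- PAL + IHP, 80 %: V = 8 × 0.0225/9.505 = 0.018937; k² = (0.018937 − 0.002075)/0.0425; k = 63.0 % (stated 62.9).
- PAL + IHP, 90 %: k = 54.1 % (stated 54).

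The stated limits are correct to within rounding.

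**Step 2: put the two allowances on one scale.** Design effect = 1 + (m − 1)ρ and k² = ρ(1 − p)/p, where ρ is the intracluster correlation (ICC). For k = 0.25 at p = 0.05, ρ = 0.0625 × 0.05/0.95 = 0.00329. The design effect is 1 + 49.4 × 0.00329 = 1.16 at the baseline cluster size and 1 + 99 × 0.00329 = 1.33 at 100 per cluster. Neither is near 2.

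**Step 3: power if the design effect of 2 applies.** Power = Φ{√[(c − 1)(p1 − p0)²/V] − 2.2414}. The article does not say how its 2 carries over to follow-up, so three readings are shown.

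- *(a) Baseline cluster size.* ρ = 1/49.4 = 0.0203; k = √(0.0203 × 19) = 62 % at p = 5 %. With the same BCV in both arms, V = 0.001375 + 0.385 × 0.0125 = 0.00619 and power for PAL alone is Φ(1.798 − 2.241) = 33 %. With the same ICC in both arms (BCV 42.7 % at p = 10 %), V = 0.00416 and power is Φ(2.193 − 2.241) = 48 %.
- *(b) Follow-up cluster size.* ρ = 1/99 = 0.0101; k = 44 %. Same BCV: V = 0.00377, power Φ(2.302 − 2.241) = 52 %. Same ICC: V = 0.00276, power Φ(2.690 − 2.241) = 67 %.
- *(c) Flat doubling of the sampling variance, no further BCV.* V = 0.00275, power Φ(2.697 − 2.241) = 68 %. Using c instead of c − 1 gives 73 %, but that variant does not reproduce the stated limits.

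| Assumption | PAL alone, same BCV | PAL alone, same ICC | PAL + IHP, same BCV | PAL + IHP, same ICC |
|---|---|---|---|---|
| BCV 25 % (protocol) | 79 % | – | >99.9 % | – |
| (a) design effect 2 at 50.4, control BCV 62 % | 33 % | 48 % | 81 % | 99.9 % |
| (b) design effect 2 at 100, control BCV 44 % | 52 % | 67 % | 97 % | >99.9 % |

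Reading (c) gives 68-73 % for PAL alone and over 99.9 % for PAL + IHP.

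**Step 4: could village clustering absorb the 2?** There are 1,360/(27 × 30) = 1.7 symptomatic people per sampled village at baseline, so little of it can sit there. Under reading (a), assumed village correlations of 0.05 to 0.3 (not in the protocol) give PAL alone 34-39 % and PAL + IHP 84-94 % with the same BCV, and 48 % and 99.9 % with the same ICC.

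**The case against.** The strongest reply has four parts.

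1. **The arithmetic is right and conditional.** All four limits reproduce, each is tied to a BCV, and 79 % at a BCV of 25 % is fairly described as close to 80 %. This stands: the fault is an inconsistent assumption, not a miscalculation.

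2. **The design effect of 2 is a generic precision allowance.** The baseline section also applies it to cough prevalence at 13,608/27 = 504 people per cluster, where the same conversion gives a BCV of about 13 %. It covers households, villages and health centres together. A reader might infer that the protocol implies a BCV of 62 %, but it does not say so. That value requires nearly all of the 2 to sit at health-centre level and to be read at the baseline cluster size. Sparse sampling within villages makes the first condition roughly true, but it remains an assumption.

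3. **The lowest figures need the same BCV in every arm.** This is the convention that reproduces the protocol's own limits. With the same ICC instead, 33 % becomes 48 % and 81 % becomes 99.9 %. A reader might infer that the PAL + IHP claim of over 90 % is wrong. The figures do not show that: power falls below 90 % only if the BCV exceeds about 54 % in both arms, and most readings stay above 90 %.

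4. **The assumptions are to be revisited after baseline.** This lessens the harm but does not make the published allowances agree. The health centres are already selected. If that leaves only more households as a lever, unlimited sampling per cluster would still cap PAL-alone power at about 42 % for a BCV of 62 % and about 74 % for 44 % (67 % and 94 % with the same ICC).

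**Conclusion.** The inconsistency is real. A BCV of at most 25 % corresponds to a design effect of 1.16 at baseline or 1.33 at follow-up, against the 2 allowed for the same outcome. If the 2 applies, PAL-alone power for 5 versus 10 % is about 33-48 %, 52-67 % or 68-73 %, depending on how it is carried to follow-up. Each of these is below the stated level, so the chance of missing a real effect is about 27-67 %, not about 20 %.

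For PAL + IHP, power remains about 81 % or higher and above 90 % on most readings. Only the worst-case wording fails, because a value described as usual is not a worst case.

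A reader might go further and conclude that a null PAL-alone result is more likely than not even if the effect is real. That follows only under reading (a); readings (b) and (c) give power above 50 %.

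The results rest on two-sided 0.025, 9 clusters of 100 symptomatic people per arm, and the standard conversion between design effect, ICC and BCV.

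**What to change.** - Use one clustering assumption for the diagnosis outcome in both the baseline precision and the follow-up power calculations.
- Restate PAL-alone power as a range, with the same BCV in both arms: 79 % at a BCV of 25 %, about 52 % at 44 %, about 33 % at 62 %.
- Delete the worst-case phrase for PAL + IHP and give its power over the same range: over 99 %, about 97 %, about 81 %.
- Update both sets of figures with the BCV observed in the baseline survey, as the sample size section already foresees.

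The change is to wording and needs no extra participants. Its cost is a less favourable stated power for one primary comparison.

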#### Data collection and management

The baseline survey will be conducted prior to randomisation and prior to intervention implementation. The follow-up survey will be conducted 1 year after intervention implementation. Data will also be gathered from health centres 1 year after the interventions have been implemented.

Measures will be taken to ensure quality and accuracy of information, which will be collected and reported; these will include: firstly, thorough training of health workers – the training content will include proper recording of diagnoses based on knowledge of presenting symptoms and signs of each condition and the differential diagnoses. In addition health care workers will also be taught about spirometry results so that they acquire understanding to help with them in interpreting spirometry results to make accurate diagnosis. Secondly, the trial clinical supervisor will routinely undertake monitoring of practice in the intervention health facilities to ensure that standards are being followed regarding practice, recording and reporting. Patient health passports, PAL registers at facilities and spirometry records will be assessed during the visits.

The data collected from health registers as digital images will be scanned into an electronic database using Teleform software (Cardiff Software, Sunnyvale, CA, USA) or, if this proves to be technically difficult; the scanned images will be double-entered by trained data entry clerks into an Microsoft Access for windows or Epi-Info 6.04 database, a free software developed by the Center for Disease Control of Atlanta in the United States of America.

All other quantitative data will be collected on pre-prepared and validated pro-formas by trained researchers. All forms completed on any given day will be checked visually at the end of the day and any data queries identified (including missing entries) will be checked with theresearchers. The data will then be double-entered onto a pre-prepared Access or Epi-Info computer database, and the original pro-formas will be stored in locked filing cabinets in a secure area within the research centre. This will serve as a data security measure and also to protect confidentiality. The computer server holding the Epi-Info databases will be backed-up daily to a second server held in an area physically separate from the primary server; a secondary back-up will also be made onto a portable disk-drive, which will be held in a locked cabinet for safety and security.

All principal investigators will be given access to the final cleaned data sets. Data will be anonymised to maintain confidentiality.

### Statistical analysis plan

The characteristics of the individuals recruited into study surveys will be summarised using means, median or proportions, as appropriate. All summary statistics will be accompanied by their standard deviations or 95 % confidence intervals, again as appropriate. Missing or invalid observations detected during this analysis will be referred back to the field-based researchers for clarification.

Effect sizes for the study outcome measures will be summarised using incidence rate ratios with their 95 % confidence intervals. Negative binomial and/or Poisson regression methods will be used to adjust these effect sizes for potential influencing/confounding factors; the influence of these factors on the effect size incidence rate ratio estimate will be reported for each factor individually and then for all factors combined. Multiple imputation methods will be used to accommodate any missing observations that could not be clarified by the field researchers.

The analyses will be conducted under the supervision and advice of [name], a senior lecturer in Medical Statistics at Liverpool School of Tropical Medicine.

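### The sample size allows 2.5 % two-sided for each of two primary comparisons, but the analysis section gives 95 % intervals for every outcome and does not carry that level forward

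*Protocol article*

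**What the plan says.** In the Protocol article, the section on estimating the impact of PAL alone and PAL + IHP states "The calculations presented below use an alpha level of 2.5" %, in place of the usual 5 %. The reason given is that there are two "primary comparisons (PAL + IHP versus control and PAL alone versus control". Sidedness is not stated.

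The design inputs are "With 9 clusters per group and 907 symptomatic individuals per study arm (100 per cluster"). For PAL + IHP the target is an intervention that "increases the proportion of symptomatic individuals with a registered diagnosis from 5 to 20" %; for PAL alone it is one that "increases the proportion of symptomatic individuals with a registered diagnosis from 5 to 10" %. Power of 80 % is claimed for PAL + IHP if the between-cluster coefficient of variation (BCV) "does not exceed 62.9" %, and for PAL alone "provided the BCV does not exceed 24.1" %. The limits for 90 % power are 54 % and 13.7 %.

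The Statistical analysis plan section says "Effect sizes for the study outcome measures will be summarised using incidence rate ratios with their 95" % confidence intervals. That sentence covers all outcome measures. The section names no test, p-value threshold or interval level specific to the two primary comparisons.

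**The concern.** A 95 % interval corresponds to a two-sided 5 % test. The level used for sizing corresponds to a 97.5 % interval. Confidence intervals are the only inferential output that the analysis section names, so readers are likely to judge each intervention by whether its interval excludes 1.

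The conflict arises when a p-value lies between 0.025 and 0.05. Such a result looks positive from the 95 % interval and fails at the level used for sizing. PAL alone is the comparison exposed to this, because the protocol itself expects its power to be only about 80 %. If the choice is not fixed beforehand, it could be made after the result is known.

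**Working it through.** **1. Which alpha the design used.** For unmatched clusters, the Hayes-Bennett formula is

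c = 1 + (z_α + z_β)² × [p0(1−p0)/m + p1(1−p1)/m + k²(p0² + p1²)] / (p1−p0)²,

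where c is clusters per arm, m is symptomatic individuals per cluster and k is the BCV. From the sample size section, c = 9, m = 100, p0 = 0.05, and p1 = 0.20 or 0.10. Solve for k.

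At two-sided 2.5 % and 80 % power, (2.2414 + 0.8416)² = 9.505.

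- 5 v 10 %: 8 × 0.0025 / 9.505 = 0.002104. Subtract (0.0475 + 0.09)/100 = 0.001375 to get 0.000729. Divide by 0.0125 and take the square root: k = 24.15 %.
- 5 v 20 %: 8 × 0.0225 / 9.505 = 0.018937. Subtract (0.0475 + 0.16)/100 = 0.002075 to get 0.016862. Divide by 0.0425 and take the square root: k = 62.99 %.

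| Comparison, power | Stated BCV limit | Two-sided 2.5 % | Two-sided 5 % (same as one-sided 2.5 %) |
|---|---|---|---|
| 5 v 20 %, 80 % | 62.9 | 62.99 | 70.06 |
| 5 v 20 %, 90 % | 54 | 54.08 | 59.52 |
| 5 v 10 %, 80 % | 24.1 | 24.15 | 30.64 |
| 5 v 10 %, 90 % | 13.7 | 13.75 | 20.56 |

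Of these, only two-sided 2.5 % per comparison reproduces the stated limits, so the multiplicity allowance is built into all four.

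**2. Family-wise error.** With equal arms sharing one control, the two contrasts correlate at 1/(√2 × √2) = 0.5 under the null. Family-wise error is 1 − P(|Z1| < z, |Z2| < z).

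| Global null, correlation 0.5 | Each at 5 % (95 % intervals) | Each at 2.5 % (97.5 % intervals) |
|---|---|---|
| Either direction | 9.07 % | 4.65 % |
| False benefit only | 4.54 % | 2.32 % |
| Either direction, if independent | 9.75 % | 4.94 % |
| Upper bound | 10 % | 5 % |

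Simulated t-tests on 9 cluster summaries per arm give 8.9 to 9.1 % and about 4.6 % for the first row.

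**3. Power for PAL alone at BCV 25 %,** the value the protocol treats as the usual upper end. The bracketed variance is 0.001375 + 0.0625 × 0.0125 = 0.002156, and √(8 × 0.0025 / 0.002156) = 3.046.

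- At 2.5 %: Φ(3.046 − 2.241) = 78.9 %.
- At 5 %: Φ(3.046 − 1.960) = 86.1 %.

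The difference, about 7 percentage points, is the chance that the two levels disagree when PAL alone has its assumed effect. For PAL + IHP at 2.5 % the same calculation gives a power above 99.9 %.

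**4. Interval width.** On the log rate-ratio scale, a 97.5 % interval is 2.2414/1.9600 = 1.14 times as wide as a 95 % interval with normal quantiles. With t quantiles on 16 degrees of freedom (9 + 9 − 2) the ratio is 2.473/2.120 = 1.17.

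**The case against.** The strongest objection is that the analysis section sets a reporting format and not a decision rule. It does not say that an intervention is judged by whether its interval excludes 1. The only significance level in the document is 2.5 %, with its reason, and 95 % intervals can be reported beside tests at 2.5 % without contradiction. A reader might infer that the trial has replaced its decision rule and will run at 9 % family-wise error; the text does not support that. This part of the objection stands and limits the finding.

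A second objection is that an article condenses the full protocol, and a separate analysis plan may settle how the level carries over. This stands only in part. The absence of testing detail is no finding, but the article itself states a level for the primary comparisons and an interval level for all outcomes, and does not reconcile them.

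Third, 9.1 % is the least favourable count: global null, both directions. Counting only false benefit gives about 4.5 %. That is fair, although the like-for-like figure at the planned level is then about 2.3 %, so the rate still roughly doubles.

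Fourth, the plain 2.5 % split is valid. A reader might infer that not using Holm is an error, but it is not: the protocol openly accepts power near 80 % for PAL alone. Holm also has a drawback. Its second step is tested at 5 %, so it can reject while the 97.5 % interval includes 1.

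**Conclusion.** The inconsistency is real and of moderate weight. The design sized each primary comparison at two-sided 2.5 %, and all four stated BCV limits confirm it; the analysis section gives 95 % intervals throughout. The rise in family-wise error from about 4.6 % to about 9.1 % is conditional. It assumes that significance is read from those intervals, that neither intervention has an effect, that errors in both directions count, and that the contrasts correlate at 0.5. It shows what the ambiguity would allow, and is not a demonstrated property of the trial. The practical consequence is confined to primary p-values between 0.025 and 0.05, most plausibly for PAL alone.

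**What to change.** State in the Statistical analysis plan section that the two primary comparisons are each judged at two-sided 2.5 % and reported with 97.5 % confidence intervals, and that 95 % intervals for secondary outcomes are descriptive. This takes a sentence or two, and the primary intervals become about 14 to 17 % wider. Sample size and stated power do not change.

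Optional improvement: test the two comparisons by Holm, the smaller p-value at 0.025 and, if that rejects, the other at 0.05. Family-wise error stays at or below 5 %. PAL-alone power rises from about 79 % to about 86 % at BCV 25 % if PAL + IHP reaches its assumed 20 %; if PAL + IHP is not rejected, PAL alone gains nothing. If Holm is adopted, state that the Holm-adjusted p-values decide, because the 97.5 % interval for the second comparison may include 1 when Holm rejects. Either choice should be fixed before the follow-up data are analysed.

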### Allocation of interventions

Each cluster (health centre with the surrounding catchment area) that has agreed to participate will be randomly allocated to one of the three trial arms using a computer-generated randomisation schedule with stratification by size of cluster. This randomisation will be performed by the trial statistician using dummy codes ‘A’ ‘B’ and ‘C’ to represent intervention and control groups; to ensure the statistician remains blinded, the identity (allocation) of ‘A’ ‘B’ and ‘C’ will be determined by a person independent of the study.

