#### Detail of the informal health provider intervention in arm 2

The intervention directed at the community level in intervention arm 2 will aim to build the capacity of informal health providers (IHPs) to recognise, counsel and refer potential TB and CAD patients in their communities.

Mapping of IHPs in the clusters allocated to intervention arm 2 will be done after randomisation. A qualitative study going on in the neighbouring district of Kasungu to explore how the communities understand IHPs by type and role will inform the trial to use the right definitions of informal health providers. During the mapping exercise distribution of IHPs will be determined prior to selection and training them in order to be within the buffer zones.

This intervention will include:Training of informal health providers in the recognition, counselling and referral of patients with chronic/persistent cough to the primary health facility.Training of informal health providers in prevention of COPD and including smoking cessation.Training informal health providers to support patients with airway diseases so that they adhere to both drug and non-drug therapies and compliance to appointments.Training of local health centre staff and health surveillance assistants to give supervisory support to informal health provider activities.Establishment of referral mechanisms between the community and the health system.

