#### Baseline survey

Data on CAD is not routinely collected in the study districts, so to inform the final sample size estimation a baseline survey will be conducted, the purpose of which will be to estimate the proportion of individuals over the age of 15 years in each cluster with (a) evidence of chronic cough-/- wheeze, and (b) a diagnosis in their health passport.

For this baseline survey, it will be assumed that for the study population:(i)the mean household size in the study area will be 4.6(ii) the proportion of individuals over the age of 15 years will be 0.52 (52 %)(iii) so the average number of individuals per household over the age of 15 years will be 4.6 × 0.52 = 2.4

As described in detail in table 1, a 3-stage sampling procedure will be used:Stage 1: a random sample of 27 clusters (health centres with surrounding catchment areas) will be selected and 9 of these randomly allocated to each study armStage 2: 30 villages will be randomly selected from each of these 27 clusters based on sampling probabilities proportional to village population again using Google Earth Pro (Google Inc., Mountain View, CA, USA) to identify villages and to estimate their sizes (total 810 villages: 270 per study arm)Stage 3: a simple random sampling procedure will be applied to select 7 households from each selected village (total 5,670 households: 1,890 per study arm)

All eligible participants in each selected household will be interviewed, giving a total sample of 5,670 × 2.4 = 13,608 individuals (4,536 per study arm); 10 % of these individuals (1,360 in total: 453 per study arm) will be expected to show evidence of chronic cough-/-wheeze.

The precision figures quoted below for this baseline survey use the approximate formula for a 95 % confidence interval ‘1.96 × standard error of prevalence estimate’. In the actual analysis, exact binomial confidence intervals will be computed, but these are asymmetric so unsuitable for presenting a simple indication of the precision levels that will be achieved.

Assuming a prevalence of 10 %, a sample of 4,536 individuals will provide an estimate of the true prevalence of chronic wheeze-/-cough in each individual study arm with a precision of ±0.87 %. Ignoring clustering effects, the 13,608 individuals in all 3 study arms combined will provide a precision of ±0.50 %; adding a design effect size adjustment of 2 to allow for clustering effects, the combined sample will have a precision of ±0.71.

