## Discussion

The trial will undertake two cross-sectional household surveys: one at the beginning of the trial, prior to randomisation of clusters, and the second after the interventions have been in place for a year. Although the intervention is health centre-based to improve quality of service the primary outcome measure will be assessed in the communities. Trial data, therefore, will have several sources including cross-sectional household surveys, clinic registers, and patient health passports. Monitoring and supervision tools will be developed to support the completeness and accuracy of these data. A subset of patients will be selected to assess quality and accuracy of diagnosis and patient management.

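### The effect estimates are to be adjusted for an open-ended set of factors, singly and then jointly, with no primary model designated and no stated role for the randomisation stratum or the baseline cluster outcome

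*Protocol article*

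**What the plan says.** The Statistical analysis plan section summarises effects as incidence rate ratios. Negative binomial and/or Poisson regression "will be used to adjust these effect sizes for potential influencing/confounding factors", and the influence of these factors on the rate ratio "will be reported for each factor individually and then for all factors combined". No factor is named, and no criterion for choosing factors is given. The Baseline survey section adds that clustering at household, village and catchment level will be handled by multi-level models, again without naming a covariate.

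Two design features bear on this:

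- **Stratum.** Under Allocation of interventions, clusters are allocated "using a computer-generated randomisation schedule with stratification by size of cluster".
- **Baseline outcome.** "The baseline survey will be conducted prior to randomisation and prior to intervention implementation", according to Data collection and management. The survey is meant "to estimate the proportion of individuals over the age of 15 years in each cluster with (a) evidence of chronic cough-/- wheeze" and, as item (b), a diagnosis in the health passport. Its only stated purpose is sample size: "to inform the final sample size estimation a baseline survey will be conducted".

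The Discussion says: "The trial will undertake two cross-sectional household surveys". The second comes a year after the interventions start. In arm 2 the informal-provider package includes "Training of informal health providers in prevention of COPD and including smoking cessation", and it also aims to encourage care-seeking.

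**The concern.** Adjusting for possible confounders one at a time and then all together is a routine from observational work. In a randomised comparison it raises three problems.

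1. **Which factors.** The wording has no limit. A factor recorded at follow-up that the intervention can change lies on the pathway from intervention to outcome, or is a consequence of the intervention. Conditioning on it can remove or distort part of the effect being estimated.
2. **Which estimate.** The scheme yields an unadjusted ratio, one ratio per factor and a fully adjusted ratio, for each of two primary comparisons. None is marked as the answer.
3. **Which covariates the design supplies.** Stratified randomisation is normally reflected in the analysis, and a pre-randomisation measure of the same outcome in all 27 clusters is the natural covariate. With 9 clusters per arm, chance imbalance between arms is a real possibility. The text gives neither variable a role.

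**Working it through.** **Part 1: what the wording permits.** Because both surveys are cross-sectional samples, the people analysed for the primary outcome are those interviewed at follow-up. Their individual covariates are therefore recorded after a year of intervention. Some, such as age and sex, cannot be affected by it. Others, such as smoking and care-seeking, are named targets of the arm 2 package. The analysis section draws no line between the two kinds.

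**Part 2: reproducing the plan's own figures.** Inputs from the sample size section: c = 9 clusters per arm; m = 100 symptomatic people per cluster; control proportion p0 = 0.05; p1 = 0.10 (PAL alone) or 0.20 (PAL + IHP); alpha 0.025, taken as two-sided because that reproduces the stated limits. The Hayes–Bennett unmatched formula is

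c = 1 + (z_a + z_b)² × [p0(1−p0)/m + p1(1−p1)/m + k²(p0² + p1²)] / (p1−p0)²,

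where k is the BCV. Solved for k:

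| Comparison | Power | Computed k | Stated |
|---|---|---|---|
| PAL alone | 80% | 24.15% | 24.1% |
| PAL alone | 90% | 13.75% | 13.7% |
| PAL + IHP | 80% | 62.99% | 62.9% |
| PAL + IHP | 90% | 54.08% | 54% |

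All four agree up to truncation. None relies on covariate adjustment.

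**Part 3: chance imbalance at the planned BCV.** With k = 0.25, the standard deviation of the difference between two arms' true mean proportions is 0.25 × 0.05 × √(2/9) = 0.0059, or 0.6 percentage points, against a PAL-alone target of 5 points.

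**Part 4: value of the baseline proportion, PAL alone, k = 0.25.**

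- Sampling term: (0.0475 + 0.09)/100 = 0.001375. Between-cluster term: 0.0625 × (0.0025 + 0.01) = 0.000781. Total 0.002156.
- Unadjusted power: Φ(√(8 × 0.0025/0.002156) − 2.241) = Φ(3.046 − 2.241) = 78.9%.
- Baseline survey: 453/9 = 50.3 symptomatic people per cluster, so about 50.3 × 0.05 = 2.5 diagnoses.
- Reliability of the observed cluster proportion: (0.25 × 0.05)² / [(0.25 × 0.05)² + 0.05 × 0.95/50.3] = 0.000156/(0.000156 + 0.000944) = 0.14.
- Share of between-cluster variance removed = ρ² × 0.142, where ρ is the true baseline-to-follow-up correlation. The document does not give ρ, so a range is assumed.

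| Assumed ρ | Variance share removed | Power |
|---|---|---|
| 0.5 | 0.036 | 79.5% |
| 0.8 | 0.091 | 80.4% |
| 1.0 | 0.142 | 81.2% |

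On a noncentral t reference (noncentrality √(9 × 0.0025/variance)) at ρ = 0.8, power goes from 76.8% (16 df) to 77.1% (14 df) using two arms. With all 27 clusters pooled it goes from 79.3% (24 df) to 80.3% (22 df). The gain is then roughly 0.4 to 1 point.

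**Part 5: value of the stratum, same setting.** The share of between-cluster variance explained by cluster size is not given. On the normal reference, without a degrees-of-freedom charge, power is 80.5%, 83.0% or 87.0% if that share is 10%, 25% or 50%. PAL + IHP stays above 99.9% throughout.

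**The case against.** The strongest reply is that the text names nothing, so it excludes nothing.

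- **Follow-up factors.** A reader might infer that the plan adjusts for factors altered by the intervention. It does not say so: smoking appears in the intervention description, not as a covariate, and a confounder in the ordinary sense is not a consequence of treatment. Measurement at follow-up does not in itself make a trait alterable. This stands: bias is permitted by the wording, not planned, and it cannot be quantified without a covariate list.
- **Stratum and baseline outcome.** A reader might infer that these are left out in favour of other factors. The document supports only that they are not named; both could be among the unnamed factors.
- **SAP detail.** Covariate lists are commonly left to an analysis plan, and one may exist. That disposes of any complaint that the list is missing. It does not dispose of the singly-then-jointly scheme, which the article states and a list of names would not change.
- **Several estimates.** The sentence can be read as one estimate plus an open account of how adjustment moves it, and it describes no selection by significance. That reading is fair, but the text does not say which estimate is the main one.
- **Power.** A large gain from baseline adjustment appears only at a BCV near 62%. That is about the tolerance limit for PAL + IHP, not a value the protocol expects; its planning figure is at most 25%. There the gain is near zero once degrees of freedom are counted.

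**Conclusion.** The point holds as a fault in a stated procedure. The article commits the randomised comparison to open-ended, factor-by-factor adjustment, without restricting it to factors beyond the intervention's reach, without designating an estimate for either primary comparison, and without giving the randomisation stratum or the baseline cluster outcome a stated role. It does not show that biased adjustment will occur, or that those two variables will be ignored.

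The case does not rest on power. At BCV 25% the baseline proportion is worth at most about 2.3 points (81.2 − 78.9) for PAL alone, under an assumed correlation of 1.0 and before any loss of degrees of freedom. The stratum is worth about 1.6 to 8 points over an assumed 10–50% of between-cluster variance. What matters more is analysing as randomised, guarding against chance imbalance with few clusters, and having one pre-specified answer per comparison. It should be corrected before the follow-up data are analysed.

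**What to change.** Replace the adjustment sentences in the Statistical analysis plan section with:

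1. One primary effect model for both primary comparisons, containing arm, cluster-size stratum and the cluster's baseline proportion with a recorded diagnosis, with age and sex optional. Clustering stays in the multi-level model already announced.
2. A statement that factors recorded at follow-up which the intervention could change, such as smoking or care-seeking, do not enter that model.
3. A statement that factor-by-factor and all-factor results are descriptive and do not answer the primary comparisons.

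The cost is a change of wording. The stratum is known from randomisation and the baseline proportion comes from a survey already planned. The model spends about two cluster-level degrees of freedom. With only about 2.5 expected diagnoses per cluster at baseline, that covariate is noisy, so the text should not promise a material precision gain from it.
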